## Abstract

**Background:**

Prostate cancer (PCa) is the most common male malignancy in the western world. Many men (40%) are diagnosed with localised low or intermediate-risk PCa, which is suitable for active surveillance (AS). AS affords careful monitoring to identify changes in otherwise non-life-threatening cancers. While AS reduces overtreatment (and quality of life impact), long-term compliance can be poor, with many men undergoing radical treatment after starting AS.

**Methods and analysis:**

Finasteride in Active Surveillance for men with low and intermediate-risk prostate cancer (FINESSE) is a prospective, open-label, two-arm, phase 3 trial, in which men with low or intermediate PCa are randomised (1:1) to receive AS with or without finasteride (5 mg once a day for 2 years). Randomisation is stratified by age and PCa risk. AS includes regular prostate-specific antigen testing, MRI scans and the offer of repeat biopsy (at 3 years, or if imaging suggests progression). Additional MRI scans and/or biopsies will be performed for biochemical or clinical indications. We aim to recruit 550 men (aged 50 to 75 years) from up to eight sites. Active outpatient follow-up will be for 3–5 years (depending on date recruited), followed by passive registry-based follow-up for up to 10 years. Primary outcome is adherence to AS. Secondary outcomes include rates and type of disease progression, treatments received (for PCa and benign prostatic enlargement), overall and PCa-specific mortality, an understanding of patients/professionals views of this approach and health-related quality of life. An external panel of experts blinded to allocation will review all AS cessation and progression events. Trial pathologist’s and radiologist’s, blinded to allocation, will review representative cases. Analysis is Intention to Treat.

**Ethics and dissemination:**

The study received Health Research Authority and South-Central Oxford Research Ethics Committee (14/12/2021: 21/SC/0349) and CTA/MHRA (29/12/2021: 21304/0274/001–0001) approvals. Results will be made available to providers and researchers via publicly accessible scientific journals.

**Trial registration number:**

ISRCTN16867955

Strengths and limitations of this studyWhile active surveillance (AS) is an established method of managing men with prostate cancer, few studies have attempted to improve compliance with this regimen.Finasteride is widely available, has a known safety profile, is well tolerated and is used in a similar patient population for benign prostate enlargement.This study will determine AS outcomes in a contemporary cohort of intermediate-risk cancers.There remains some scepticism about the role of pharmacological prostate-specific antigen manipulation for AS patients.Pre-biopsy MRI may reduce the pool of eligible men and hamper recruitment.

## Introduction

 Prostate cancer (PCa) is the most common male malignancy in the western world.^1^ Prostate-specific antigen (PSA) screening of asymptomatic men has been used to reduce mortality from the disease. However, most men diagnosed through this route have clinically localised disease and may not benefit from treatment as their cancers are indolent, with a long natural history, or metastatic at diagnosis.^2^ There has yet to be a universally accepted screening programme for PCa and most men are diagnosed through ‘case-finding’ using PSA testing for lower urinary tract symptoms or known risk factors (eg, family history). The detection and radical treatment of PCa that would not impact the patient during their lifetime represents overdiagnosis and overtreatment, respectively.^3^ One solution to overtreatment is the use of active surveillance (AS).^4^ This strategy selects men with indolent appearing cancers and monitors tumour growth. Radical treatment is reserved for men whose tumours progress biochemically, clinically or radiologically.

In men with low-risk PCa undergoing AS, the risk of disease-specific mortality is small (eg, 0.3% at 8 years and lower than that from competing diseases^5^). AS is popular among men with localised PCa^6 7^ and recommended by the National Institute for Clinical Excellence (NICE) guidelines in the United Kingdom (https://www.nice.org.uk/guidance/ng131). However, there are concerns regarding the accuracy of PCa risk stratification and the reliability of monitoring tools.^8^,^10^ Clinicians and patients fear that deferring radical treatment could reduce the chance of cure and lead to higher morbidity.^10 11^

Between 50% and 70% of men starting AS will receive either radical or palliative treatment over the following 10 years.^12^,^14^ In most men, radical treatment is initiated due to either a rising PSA or changes in Gleason grade on biopsy. Both are surrogate measures for disease progression. Many men are reluctant to undergo multiple biopsies and so most AS programmes are heavily reliant on PSA kinetics. For example, 25% of men in the Gothenberg screening trial^14^ and 43% of men in the Toronto trial who started AS received radical treatment due to a rising PSA alone.^4^ PSA values reflect benign enlargement and inflammation within the prostate^13^ as well as cancer growth. Therefore, many men with rising PSA values may not have disease progression and may not need radical treatment. For example, 65% of men within the PRIAS study^13^ and 72% in a large US series^15^ had favourable histology at radical prostatectomy after a period of AS. Within the ProtecT RCT, 50% of men randomised to monitoring received radical treatment with a <2% mortality rate at 10 years,^12^ highlighting the potential for overtreatment.

Various approaches have been tried to improve compliance with AS, including pharmacological interventions. The REDEEM study group randomised 302 men with low-risk PCa to 0.5 mg daily Dutasteride or placebo.^16^ At 3 years, the Dutasteride group had 10% fewer men with disease progression (defined as increasing cancer burden on biopsy or undergoing radical treatment). The ENACT study group randomised 227 men with low or intermediate-risk PCa to AS with or without 160 mg daily Enzalutamide.^17^ The addition of Enzalutamide reduced progression (pathological or therapeutic) by 46% at 12 months, although no difference was present at 2 years, there were side effects with this agent and its cost poses financial challenges to healthcare providers (especially if for long term AS regimens).

Contemporary AS cohorts include many men with intermediate-risk PCa, as MRI may have changed the spectrum of PCa’s diagnosed. Many men with small, low risk PCas are often no longer diagnosed either because they do not have a biopsy or there is less random prostate sampling.^18^,^20^ Within the PRECISION trial, 38% of men with mpMRI-guided biopsy (vs 24% in ultrasound scan (USS)-guided biopsies) had Gleason 3+4 PCa.^18^ Van der Leest *et al* found that mpMRI-guided biopsy reduced the rate of insignificant PCa diagnosis from 25% to 14%.^19^ Therefore, the focus to improve the care of men with PCa is shifting to using AS in men with intermediate-risk PCa.^21^,^26^ This population is common and includes more men with lethal cancer than in the low-risk cohorts.^5^ Thus, AS regimens need to combine safety with tolerability and adherence. Improving AS was the highest research priority selected in the recent NICE guidelines for PCa management (Question number 1: What is the most suitable surveillance protocol? (https://www.nice.org.uk/guidance/ng131). Given the positive signals from the REDEEM and ENACT trials, this study aims to test if the drug Finasteride can increase men’s adherence to AS and reduce radical treatment rates, using a more contemporary cohort.

## Methods and analysis

### Design

Finasteride in Active Surveillance for men with low and intermediate-risk prostate cancer (FINESSE) is a randomised, prospective, non-blinded, open-label, parallel group, phase 3 trial. Men will be randomised 1:1 to receive AS plus finasteride (5 mg) for 2 years or AS alone.

### Randomisation and population

Randomisation is through a web-based tool bespoke to the King’s Clinical Trials Unit. Once participants have completed a signed consent form (online supplemental file 1), for example, Finesse Consent form, V.5.0 from 27 March 2024, their data will be stored on the system. The randomisation process is at the individual level using the method of permuted block randomisation with block sizes stratified by PCa risk (low vs intermediate) and participant age (<65 vs >65 years).

### Blinding

This is an open label study. Both participants and clinicians will be aware of the study arm to which they are randomised. While test results, for example, MRI scans and PSA values can make it obvious that a participant is taking finasteride, the following will be blinded (not informed) to treatment allocation:

Lead Trial Radiologist responsible for reviewing MRI scans.Lead Trial Pathologist responsible for reviewing histopathology.Independent PCa Progression Review Panel, made up of three urologists.

### Study setting

The FINESSE trial is recruiting in secondary care sites. The trial is funded by Yorkshire Cancer Research, a charity whose remit is to fund research which will save lives in Yorkshire, and so initial sites have been established within the Yorkshire region. Non-Yorkshire centres will be included to expedite recruitment. Eligible patients are identified by secondary care clinicians (urologist) in outpatient clinics and multidisciplinary team meetings. Research nurses will support the screening, consent and follow-up processes.

### Recruitment

We aim to recruit 550 men over 24 months. The trial management group will monitor this in real-time and recommend action if recruitment is behind projections (such as opening additional sites, extending recruitment duration or adjusting eligibility (eg, removing biopsy restrictions, increasing the time since diagnosis)). Patient and public involvement in research (PPI) representatives and behavioural scientists will be involved from the outset to ensure that the research questions and study design are relevant to the needs of patients with PCa, to inform the patient facing literature, and to facilitate effective recruitment. Patients may self-refer by contacting their local FINESSE investigator. Informed consent will be obtained by recruiting physicians (onlinesupplemental files 1^2^).

### Eligibility criteria

Male subjects aged 50–75 years, with an estimated life expectancy of 10 years or more, who have opted for AS as their preferred PCa management option.Willing and able to provide written informed consent, or if appropriate, have an acceptable individual capable of giving consent on their behalf.Fit enough and suitable for radical treatment.Eastern Oncology Performance status ≤1.A histological diagnosis of Gleason grade group ≤2 (ie, Gleason grade 3+3=6 or 3+4=7) PCa within the last 6 months.Radiological stage ≤T2 b cN0 cM0 as defined by mpMRI imaging within the last 6 months (from the date of the mpMRI scan to the date of the patient’s randomisation). A copy of the mpMRI scan and report-confirming eligibility will be required.PSA ≤20 ng/mL. The result must be within 3 months of the date of the patient’s randomisation.PSA density ≤0.2 ng/mL/mL. The result must be within 3 months of the date of the patient’s randomisation.Biopsy criteria (via either transrectal or transperineal routes) within the last 6 months of the patient’s randomisation date):If targeted biopsy, then the maximum cancer core length is ≤10 mmIf targeted and systematic sampling biopsy, then the maximum cancer core length should be ≤10 mm, and ≤2 or ≤15% of non-targeted cores involved with cancer.If non-targeted biopsy (ie, USS template or sampling irrespective of lesions), then maximum cancer core length is ≤10 mm AND ≤3 or ≤20% of total number of cores involved with cancer.

### Ineligibility criteria

Previously received treatment for PCa (including radiotherapy, hormone therapy, brachytherapy or surgery). Of note, men who have received treatment for benign prostate enlargement are eligible.Current or recent (≤12 months) treatment with finasteride or dutasteride.Currently enrolled or has been a participant within the last 30 days, in any other investigational drug or device study.Men not willing to comply with the procedural requirements of this protocol.Known allergy/sensitivity to or intolerance of finasteride or dutasteride.Known allergy to any excipients of finasteride.Any malignancy (other than non-melanoma skin cancer and/or PCa) that has not been in complete remission for 5 years.Any serious coexistent medical condition that would make repeat prostate biopsy hazardous.All contraindications to finasteride including concomitant therapy with any medication that may interact with finasteride.Any rare hereditary problems of galactose intolerance, total lactase deficiency or glucose–galactose malabsorption.Men trying for a baby or with a pregnant partner.High-risk disease.

### Usual care: AS

Men randomised to usual care will receive AS (see figure 1). Patients will not receive a placebo, as PSA and MRI changes make masking impossible, blinding PSA data would be impractical since men may actively seek PSA tests outside the study, it is ethical that control participants experiencing any side effects, for example, erectile dysfunction, know they are independent of the treatment, participants unaware they are taking finasteride may opt for radical treatment earlier, and placebo controlled trials are expensive. Concerns regarding PSA changes or digital rectal examination changes will lead to MRI scans outside the schedule. Changes in MRI and PSA will lead to either a rebiopsy (to detail histological grade) or radical treatment. Radical treatment without radiological or pathological evidence of progression is discouraged but not prohibited.

**Figure 1 F1:**
[figure not shown]
Recruitment and participant flow within the Finasteride in Active Surveillance for men with low and intermediate-risk prostate cancer (FINESSE) study. Follow-up within active surveillance includes PSA testing, MRI scans and the offer of a repeat biopsy (times in months (m) shown). ^a.^ Strongly recommended. ^b.^ Offered as a routine to all men. Also strongly recommended for changing MRI appearance and/or where indicated by the MRI scan. PSA, prostate-specific antigen.

### Finasteride plus AS

Men randomised to the intervention group will receive finasteride (oral 5 mg) to be taken once a day for 2 years, in addition to AS (as above). Participants will be prescribed finasteride on a 3 monthly basis and this will be dispensed from their recruiting hospital pharmacy. Compliance will be measured using pill counts and patient questionnaires.

## Study aims

To understand whether the addition of finasteride to AS increases adherence in men with low/intermediate-risk PCa.To understand the tolerability and compliance with finasteride within an AS regimen.To understand whether the addition of finasteride to AS reduces disease progression in these men.

## Objectives and outcomes

The primary and secondary objectives, with matching outcomes, are detailed in table 1 and box 1. We will also detail health-related quality of life, over time, using validated Patient Reported Outcome tools, including decision regret and conflict findings (table 2).

**Table 1 T1:** Primary objectives and outcomes within the FINESSE trial

Objectives	Outcome measures	Timepoint(s) of evaluation of this outcome measure (if applicable)	Additional information
**Primary objective:**To compare adherence with AS in men with low or intermediate PCa with and without 2 years of finasteride during follow-up of between 3 and 5 years from randomisation.Adherence is defined as men who have received neither radical nor palliative treatment, and have remained under surveillance, at each timepoint.	Rate of either radical prostatectomy, radical radiotherapy, brachytherapy or prostate-cancer targeted treatment. Rate of use of systemic therapies. Rate of use of androgen deprivation therapy. Rate of other treatment for PCa. Rate of participant death from PCa. Rate of men discontinuing AS for any other reason.	All cessation from AS events from participants during follow-up of between 3 and 5 years from randomisation, will be included in the first analysis. Later analysis will use passive follow-up (up to 10 years after trial closure).	Rates in each arm will be measured by patient self-reporting. Participants who are lost to follow-up, or who die of a cause unrelated to PCa will be taken as censored.

ASactive surveillancePCaprostate cancer

Box 1Secondary objectives and outcomes within the Finesse trial.Outcome measuresTime until cessation of AS due to initiation of:ADT and/or chemotherapy.Radical prostatectomy.Radical radiotherapy.Timepoint(s) of evaluation of this outcome measure (if applicable):All occurrences of cessation of AS events due to (1) ADT initiation, chemotherapy, (2) radical prostatectomy (3) radical radiotherapy, (4) other treatment including watchful waiting and (5) death from prostate cancer during participant follow-up, 4 years on average, will be included in the analysis.The listed reasons for AS cessation will be treated as competing events. Cumulative incidence plots will be presented with a curve for overall AS cessation and for cessation for the individual post-AS treatment.To measure prostate cancer progression.Outcome measuresProgression is defined as either:Increase in MRI stage from T2a to ≥T2 c, T2b to ≥T2 c, or T2x to ≥T3 b.^27^Increase in grade from gleason 3+3 to ≥3+4 or 3+4 to ≥4+3.Radical Prostatectomy histology revealing grade ≥4+3 or stage ≥T3 a.PSA progression defined as ≥25% increase from the highest prerandomisation PSA value.Radiological confirmation of metastatic prostate cancer including identification via bone and/or PSMA PET scans.Clinical record of cancer progression.Clinical record of the initiation of palliative care.Death from prostate cancer.Clinical digital rectal examination (DRE) deterioration*.Extraprostatic disease.(note *DRE results alone will not be considered a definitive endpoint).Timepoint(s) of evaluation of this outcome measure (if applicable):To measure PCa mortality.Outcome measuresParticipant death from PCa.Timepoint(s) of evaluation of this outcome measure (if applicable):All deaths from PCa occurring during the 3–5-year follow-up of the study will be analysed.To study the changes in MRI appearances of the prostate over time in men with/without finasteride.Outcome measuresbpMRI/mpMRI scan results at baseline (the diagnostic MRI), 12 and 36 months (please note, a 36-month MRI scan is strongly recommended).Timepoint(s) of evaluation of this outcome measure (if applicable):Baseline, 12 and 36 months.Additional information:We will record:Prostate volume from (height, width, length).PCa stage: using the Prostate Imaging Reporting and Data System (V.2) and Tumour, Nodes, Metastasis staging.PCa size: taken as the maximum diameter on an axial slice from the MRI acquisitions.The pMRI/mpMRI images will be quality controlled centrally by the Lead radiologist. Full details can be found in the FINESSE Radiology Manual.To understand the views of patients and healthcare professionals regarding the use of finasteride within AS for this disease.Outcome measuresSemistructured one-to-one interviews led by a trained interviewer, with selected individuals during the follow-up phase.Timepoint(s) of evaluation of this outcome measure (if applicable):Months 48– 60To measure the rate of intervention for symptoms related to benign prostate enlargement:Defined as the use of oral medication (such as alpha blocker, PDE5 inhibitor or anti-cholinergic) or endoscopic prostate surgery (such as Transurethral resection of the prostate (TURP), Urolift, Green light laser TURP, steam treatment, Holmiun Laser Encucleation of the Prostate (HOLEP) or similar).Outcome measuresPatient self-reporting.Timepoint(s) of evaluation of this outcome measure (if applicable):All symptoms during the follow-up of between 3 and 5 years until trial end.Additional information:Determined from new prescriptions for oral medication (such as alpha blocker, PDE5 inhibitor or anti-cholinergic) or the participant undergoing a prostate surgery for benign enlargement (such as TURP, Urolift, Green light laser TURP, steam treatment, HOLEP or similar).Overall (all cause) mortality.Outcome measuresDeath electronic Case Report Forms (eCRF) completed by sites.Timepoint(s) of evaluation of this outcome measure (if applicable):All deaths during the follow-up of between 3 and 5 years until trial ends.Additional information:Cause of death will be decided by note review (and CRF completion) and death certificates.

**Table 2 T2:** Schedule of events for quality-of-life measures (collected through eCRFs (electronic Case Report Forms)) during the FINESSE trial

		Treatment phase (years 1–2)									Follow-up phase (years 3–5)						
		Timepoint in months (visit can be±2 weeks).															
	Completed by participants on FINESSE web-based EDC, (REDCap)	Randomisation	3	6	9	12	15	18	21	24	30	36	42	48	54	60	Early withdrawal
Quality of life measures	EQ-5D-5L	x	x	x		x		x		x		x		x		x	x *†
	EORTC QLQ C30	x	x	x		x		x		x		x		x		x	x *†
	EPIC	x	x	x		x		x		x		x		x		x	x*†
	EORTC QLQ FA12	x	x	x		x		x		x		x		x		x	x*†
	Memorial Anxiety Scale Prostate Cancer	x	x	x		x		x		x		x		x		x	x*†
	Depression Anxiety Stress Scales (DASS) 21	x	x	x		x		x		x		x		x		x	x*†
Decision-making measures	Decisional Conflict Scale	x				x				x		x		x		x	x*†
	Subjective Decision Quality	x				x				x		x		x		x	x*†
	Decisional Regret	x				x				x		x		x		x	x*†
	Decisional Involvement	x				x				x		x		x		x	x*†
Adherence	Voils DOSE-Non adherence measure		x	x	x	x	x	x	x	x							x ‡

* Where a participant stops treatment and/or trial participation early, due to radical treatment, they will continue to receive these questionnaires for completion, for the remainder of their intended period of follow-up, providing they consent to do so. The exception for this group is the ‘Decisional Conflict Scale’ which will not be assessed again, and the decisional involvement scale which will only be administered once more, post radical therapy.

† Where a participant stops treatment and/or trial participation early, for any reason other than radical treatment, they will continue to receive these questionnaires for completion, for the remainder of their intended period of follow-up, providing they consent to do so.

‡ If the participant is still on treatment at the point of early withdrawal, one final Voils DOSE-Nonadherence measure—Extent Scale will be sent for completion.

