## Ethics and dissemination

### Approval, protocol amendments, consent

The study received approval from the Health Research Authority and South-Central Oxford Research Ethics Committee (14 December 2021: 21/SC/0349) and CTA/MHRA (29/12/2021: 21304/0274/001–0001). The study is sponsored by Sheffield Teaching Hospitals NHS Foundation Trust. The sponsors have no role in the collection, interpretation or dissemination of the trial findings. The protocol will be submitted by those delegated to do so, to the relevant Research and Development department of each participating centre. A copy of the local Confirmation of Capacity and Capability and of the Patient Information Sheet and Consent Form, on local headed paper should be forwarded to the Cancer Prevention Trials Unit (CPTU) before participants are entered. An agreement will be in place between each centre and the CPTU setting out respective roles and responsibilities.

Approval for release of Hospital Episode Statistics (HES) data and access to data processed by the National Cancer Registration and Analysis Service will be obtained from NHS Digital or replacement body at the time of application. The Trial Master File will hold all approvals and relevant communications with the aforementioned bodies and be maintained by the CPTU.

Informed consent will be obtained prior to randomisation (online supplemental file 1, Finesse Consent form).

Results will be made available to providers and researchers via publicly accessible scientific journals and presentations at academic meetings. Results will be shared with patient groups through the funders (Yorkshire Cancer Research) and relevant patient groups.

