### Confidentiality and access to data

The investigator(s)/site(s) will permit trial-related monitoring, audits, REC review and regulatory inspection(s), providing direct access to source data and documents. Study participants will be informed of this during the informed consent discussion. The process will include participants being asked to consent to provide access to their medical notes and/or to any online registries that contain information related to their diagnosis. Access to data will be limited to the minimum number of individuals necessary for quality control, audit and analysis.

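### Table 1 takes the primary outcome of an open-label trial from patient self-report, which cannot cover prostate cancer death and conflicts with the record-based death sources in Box 1

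*Protocol article*

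**What the plan says.** Table 1 (Objectives and outcomes) counts a man as adherent while he stays under surveillance and has had neither radical nor palliative treatment. The events that end adherence are the listed cancer treatments, prostate cancer death ("Rate of participant death from PCa") and leaving AS for any other reason. The column for additional information then states: "Rates in each arm will be measured by patient self-reporting". No other source is named for the first analysis. Passive follow-up is assigned to a later one.

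Other sections bear on this:

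- Blinding: "Both participants and clinicians will be aware of the study arm to which they are randomised". The lead radiologist, the lead pathologist and the progression panel of three urologists are not told the allocation.
- Box 1, under overall mortality: deaths come from forms completed by sites, and "Cause of death will be decided by note review (and CRF completion) and death certificates".
- PCa progression panel: independent urologists review the cases of progression and of AS cessation.
- Data collection, monitoring and harms: one system holds the electronic case report forms (eCRFs); another holds participant surveys and registry data.
- Approval, protocol amendments, consent: "Approval for release of Hospital Episode Statistics (HES) data and access to data processed by the National Cancer Registration and Analysis Service will be obtained".
- Confidentiality and access to data: the process includes "participants being asked to consent to provide access to their medical notes and/or to any online registries".
- Procedure(s) to account for missing or spurious data: men who withdraw or are lost are censored at their last visit or when withdrawal is notified.

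**The concern.** The primary analysis compares time to an event. As Table 1 is worded, that event is known only if a man who knows his arm reports it. Three things follow.

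- The rule cannot work for one of its own components, prostate cancer death, and it disagrees with Box 1 on where that information comes from.
- A treatment that is never reported is not counted, and the man contributes event-free time instead. If this happens equally in both arms, events and power are lost. If it differs by arm, the hazard ratio is biased.
- The panel's masking protects how a known case is classified. Nothing in the article says that the panel searches for cases that nobody reported.

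The conditions for unequal reporting exist. For two years the finasteride arm receives three-monthly prescriptions dispensed at the recruiting hospital, and the control arm does not. Whether this changes reporting, and in which direction, is not known.

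**Working it through.** **Sources side by side.** For prostate cancer death, Table 1 says self-report, while Box 1 says site forms, notes and death certificates. Both cannot be the source, and the first is impossible. For treatments, Table 1 says self-report only, although eCRFs, access to notes, and hospital and registry data all appear elsewhere in the article without being tied to the first analysis.

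**The plan's own figure.** The sample size does not depend on this point, but it fixes the scale for power. The inputs from the Sample size section are a hazard ratio (HR) of 0.65, 50% control events, 90% power and two-sided alpha of 0.05.

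- Freedman events: (1.960 + 1.282)² × (1.65/0.35)² ≈ 234.
- Finasteride event proportion: 1 − 0.5^0.65 = 0.363. Mean of the two arms: 0.431.
- N = 234/0.431 ≈ 542.5, or about 271 per arm. This matches the stated 271.

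**Effect of incomplete capture.** The article gives no capture rates, so every rate below is an assumption. Let p be the true event proportion in an arm and s the share of those events that is captured (C control, T finasteride). Then

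observed HR = ln(1 − sT·pT) / ln(1 − sC·pC).

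*(a) Cessation rates of 20% and 10%, as in the first sentence of the Sample size section*

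| True proportions (C, T) | True HR | Capture 95% C, 85% T | Capture 85% C, 95% T |
|---|---|---|---|
| 20%, 20% | 1.00 | ln(0.83)/ln(0.81) = 0.88 | ln(0.81)/ln(0.83) = 1.13 |
| 20%, 10% | ln(0.90)/ln(0.80) = 0.47 | ln(0.915)/ln(0.81) = 0.42 | ln(0.905)/ln(0.83) = 0.54 |

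For the 0.88 case, captured events are 275 × (0.19 + 0.17) = 99. The expected log-rank statistic is |ln 0.884| × √(99/4) ≈ 0.61, so a nominal 5% test rejects about 9% of the time.

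*(b) The inputs that generate the sample size: 50% control events, HR 0.65, 275 per arm, Schoenfeld power*

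| Equal capture in both arms | Events | Power |
|---|---|---|
| 100% | 237 | 91% |
| 95% | 225 | 89% |
| 90% | 214 | 86% |
| 80% | 190 | 78% |

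With no true effect and 50% events in both arms, capture of 100% on control and 95% on finasteride gives an apparent HR of 0.93 and about 9% rejection. Capture of 100% and 90% gives ln(0.55)/ln(0.50) = 0.86 and about 22% rejection. The reverse imbalances give 1.08 and 1.16.

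The Sample size section states both sets of rates, so both are shown. The pattern is the same: equal loss costs power and barely moves the HR, while unequal loss shifts it in whichever direction the imbalance runs.

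**The case against.** The strongest reply is that one line in a table is being read as the whole ascertainment system. The article describes outpatient follow-up, trial eCRFs, site and central monitoring, direct access to source data, and censoring tied to attended visits. Self-reporting may mean no more than what a man tells staff in clinic, and the full protocol may name site forms. This is possible. But Table 1 makes a positive statement about the primary outcome, so if sites do capture the events, it misdescribes the endpoint and still needs correcting.

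Second, prostatectomy and radiotherapy are major, objective events. Men are unlikely to leave them out, and the actual bias may be small. This stands, and it is why the figures above show sensitivity and not expected bias.

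Third, the death component will be rare. The Introduction cites mortality below 2% at 10 years in a monitored cohort; as a rough ceiling, 2% of 550 is 11 deaths over ten years, and the first analysis covers three to five. This also stands. The contradiction over deaths is a flaw in the definition more than a threat to the estimate.

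A reader might go further in three ways that the article does not support:

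- That records of every treatment are already planned. The article plans access to hospital, registry and notes data but does not say that they capture everything, and approval is still to be obtained.
- That hospital and registry data are expressly kept for later analysis. Table 1 assigns passive follow-up to the later analysis, and the abstract calls that follow-up registry-based, but nothing bars these data from the first analysis.
- That masking gives no protection. The panel is blinded and limits misclassification of reported events; the gap is in events that go unreported.

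**Conclusion.** The point holds in a limited form. Table 1 names patient self-report as the only source for the primary outcome of an open-label trial. That source cannot apply to prostate cancer death and does not agree with Box 1. Blinded review of known cases does not close the gap for unreported ones.

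The size of any bias cannot be found from the article. Under assumed capture of 95% on control and 85% on finasteride, with 20% true events in both arms, a true HR of 1.00 would appear as 0.88; the reverse imbalance gives 1.13. Equal capture of 90% in both arms would lower power from about 91% to 86% on the sample-size inputs. No capture rate or direction is documented, so these are illustrations. The change is worth making because the better sources are already part of the trial and the article describes recruitment as still active.

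**What to change.** Amend Table 1 so that, for the first analysis:

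- treatment events and their dates come from site eCRFs and medical notes;
- prostate cancer deaths come from the sources that Box 1 already names: site death forms, note review and death certificates;
- both are cross-checked at the primary data cut against the planned Hospital Episode Statistics and cancer registration data, for men who consented and where access is granted;
- a patient's report prompts a records check, and remains a valid source in its own right for leaving AS without treatment, which may leave no treatment record.

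The cross-check should not be promised for all randomised men, because consent is sought for notes and/or registries and data release still needs approval. The same capture procedure should apply in both arms.

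The cost is a short amendment, some extra checking by sites and the trials unit, and waiting time for an extract at the primary data cut.
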